It is currently unknown how many primary care patients are at an unrecognized early stage of chronic kidney disease and who many of them are undertreated in the Netherlands.

Unlike other chronic diseases that have established screening strategies, no consensus on the early identification and intervention for CKD is reached by governments and health systems. Guidelines to manage and evaluate early CKD are available but not universally adopted (15). The 2019 international conference from the Kidney Disease Improving Global Outcomes (KDIGO) with clinicians and scientists delivered guidelines for CKD screening. The group concluded that efforts for early detection of CKD should first be implemented among people with hypertension, Diabetes Mellitus and cardiovascular disease.

General practitioners and pharmacists are frontline health care professionals who play an important role in early identification of patients at risk of CKD. Cardiovascular risk management programs are developed by multidisciplinary teams in the Netherlands that provide recommendations on how to estimate the patient's cardiovascular risk profile (7). Cardiovascular risk assessment, including albuminuria testing should be part of routine care in the Netherlands as stated in the Dutch guidelines. However, only a minority of patients were found to be tested on albuminuria in general practice (16).

A public health benefit of identifying subjects with mild to moderate CKD in the early stages is suggested. Insights in the prevalence of elevated albuminuria, the proportion unrecognized chronic kidney disease and the proportion of high-risk subjects with optimal treatment are essential to evaluate the (cost-) effectiveness of a targeted screening in primary care. Therefore, the aim of the current study is to evaluate if and how early identification of CKD by targeted screening using albuminuria-levels is feasible in primary care, to optimally discover and treat subjects with elevated albuminuria.

[figure not shown]

Figure 1. Prevalences of different risk factors for chronic kidney disease (obesity, Diabetes Mellitus, hypertension, lipid disorders and cardiovascular disease) reported in the Dutch population with reported and unknown prevalences of elevated albuminuria in subgroups of patients with (combinations of) risk factors.

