#### Targeted screening via general practitioners

General practitioners will select eligible subjects for albuminuria screening from subjects' electronic medical records, based on the presence of risk factors for elevated chronic kidney disease. Using a VIPlive selection report, subjects will be selected based on recording of one or more of the following:

3. An ICPC code for Diabetes Mellitus
4. An ICPC code for cardiovascular disease, including hypertension
5. An ICPC code for lipid disorders
6. An ICPC code for obesity or a calculated BMI  $\geq 30$  kg/m^2, based on height and weight

If albuminuria status was recently (within 18 months) assessed by the general practice and was found to be 'normal' (< 3.0 mg/mmol), subjects will not be invited for albuminuria screening. All other subjects with an increased risk of chronic kidney disease will be invited by their general practice to participate.

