#### Albuminuria screening using PeeSpot

Selected subjects will receive an invitation to participate in the screening survey from their pharmacy or general practice by postal mail, including an informational letter about the study, an informed consent form, a short questionnaire to be completed (Appendix 16.1)

and a urine collection device (PeeSpot) with instructions. The participant will be asked to send the signed informed consent form and completed questionnaire and the collected urine to the General Practitioners Research Institute (GPRI) by postal mail (without costs). If the laboratory measures 'normal' albuminuria ( $<3.0$  mg/mmol), GPRI will inform the subject. In case of elevated albuminuria ( $\geq 3.0$  mg/mmol), GPRI will be informed to send a second PeeSpot for a confirmational measurement if informed consent has been received. If this second measurement is also elevated ( $\geq 3.0$  mg/mmol), subjects will be invited for an elaborated screening visit performed by GPRI (phase 2). A second confirmational measurement of elevated albuminuria will not be required when a recent (within 11 months) measurement performed by the general practice also indicated elevated albuminuria.

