### 5.3 Exclusion criteria

- Inability to understand and sign the informed consent form
- Pregnancy
- Know normal (<3mg/mmol) albuminuria status with 18 months prior

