#### 9.1.2 Secondary endpoints

1. Unrecognized chronic kidney disease, defined as elevated albuminuria, not reported by the subject and not previously recorded in electronic medical records of the subjects' general practice or pharmacy.
2. Persistent elevated albuminuria, defined as elevated albuminuria persisting despite good adherence to treatment with RAS-inhibitors for at least 6 weeks prior to elevated albuminuria assessment (score  $\geq 4$  on the Medical Adherence Report Scale (MARS)) (Appendix C, paragraph 16.3).
3. Change in frequency of cardiovascular risk factor monitoring, defined as the difference between the frequency of cardiovascular risk factor monitoring in participants 3 years before and 6 months after targeted albuminuria screening.
4. Changes in cardiometabolic drug prescriptions, defined as changes in any prescription for cardiovascular disease or CKD 6 months after targeted albuminuria screening compared to three years before.

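### The 18-month normal-UACR filter removes tests from half of the 3-year baseline in GP-route participants and biases the before/after monitoring rate upward

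*Protocol*

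**What the plan says.** Protocol section 9.1.2 (and the Summary) sets secondary endpoint 3 as the "difference between the frequency of cardiovascular risk factor monitoring in participants 3 years before and 6 months after targeted albuminuria screening". The contrast is within participants and names no comparison group.

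Section 4.1, on recruitment through general practitioners, sets the filter: "If albuminuria status was recently (within 18 months) assessed by the general practice and was found to be 'normal" (below 3.0 mg/mmol), then "subjects will not be invited for albuminuria screening". Everyone else at risk stays in: "All other subjects with an increased risk of chronic kidney disease will be invited by their general practice to participate". Section 5.3 repeats the filter as an exclusion: "Know normal (<3mg/mmol) albuminuria status with 18 months prior". Elevated results do not exclude. A second PeeSpot is waived "when a recent (within 11 months) measurement performed by the general practice also indicated elevated albuminuria".

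Section 2 treats albuminuria testing as one component of cardiovascular risk assessment: "Cardiovascular risk assessment, including albuminuria testing should be part of routine care in the Netherlands". It adds that "only a minority of patients were found to be tested on albuminuria in general practice".

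Section 4.3 extracts data on all who qualified, whether or not they took part, and compares the two groups over the six months after screening. Section 11 summarises monitoring as numbers and percentages with 95% confidence intervals. It names no time scale, no comparator and no allowance for the filter.

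**The concern.** The eligibility rule selects on part of the outcome, inside the outcome's own baseline window. A GP-route participant cannot have a normal recorded UACR in the later half of the three baseline years. The six months after screening carry no such condition. People chosen because they lacked a recent normal test will go back to their usual testing rate, so a per-time comparison shows an increase that screening did not cause. Changing the counts to rates does not remove this, because the missing tests are still missing.

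The Summary lists a change in monitoring after screening among the study's novel aspects, and section 4.3 is built around it. An artefact in the hoped-for direction would be hard to tell from a real effect. Both sides of the problem, the filter and the endpoint definition, are fixed in the protocol, so this is not a detail that an unseen analysis plan would normally settle.

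**Working it through.** The protocol gives no rate, expected change or precision for this endpoint, so there is no figure of its own to reproduce. The check asks what the contrast shows when screening has no effect.

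**Step 1, overlap.** Filter 18 months (sections 4.1, 5.3); baseline 36 months (section 9.1.2). 18/36 = 50% of the baseline is affected.

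**Step 2, assumptions (none is in the documents).** Each person's testing rate is constant over time. p is the share of UACR tests that are elevated and q = 1 − p the share that are normal. f is the share of monitoring contacts that include a UACR test. Mean testing rates are 0.3 to 1.0 per year.

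**Step 3, UACR tests only, result varying from test to test.** Half the baseline loses its normal tests, so

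ratio after/before per person-year = 1/(1 − q/2) = 2/(1 + p).

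- p = 5%: 2/1.05 = 1.90
- p = 10%: 2/1.10 = 1.82
- p = 20%: 2/1.20 = 1.67

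**Step 4, UACR tests only, each person fixed as normal or elevated.** Normal persons pass the filter only if untested for 1.5 years, with probability exp(−1.5λ) at a common rate λ; elevated persons always pass. Among those selected, the share normal is w = q·exp(−1.5λ)/[q·exp(−1.5λ) + 1 − q]. Their baseline rate is halved, so the ratio is 1/(1 − w/2). If rates differ between persons (gamma, shape 1, mean λ), let g = q/(1 + 1.5λ)²; the ratio is then (g + 1 − q)/(g/2 + 1 − q).

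| Elevated share | λ per year | Common rate | Rates differ |
|---|---|---|---|
| 10% | 0.3 | 1.74 | 1.68 |
| 10% | 1.0 | 1.50 | 1.42 |
| 20% | 0.3 | 1.56 | 1.49 |
| 20% | 1.0 | 1.31 | 1.24 |
| 50% | 0.3 | 1.24 | 1.19 |
| 50% | 1.0 | 1.10 | 1.07 |

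First row: exp(−0.45) = 0.638; w = 0.574/0.674 = 0.852; 1/(1 − 0.426) = 1.74.

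**Step 5, all monitoring.** With results varying by test, the ratio is 1/(1 − f·q/2).

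- f = 0.1, q = 0.75 to 0.90: 1.04 to 1.05
- f = 0.5, q = 0.75 to 0.90: 1.23 to 1.29

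Simulation with fixed personal status, q = 0.8 to 0.9, gives about 1.04 at f = 0.1 and 1.11 to 1.17 at f = 0.5. Monitoring independent of UACR visits shows a ratio of 1.00.

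**Step 6, the endpoint as a difference.** At 0.3 tests per year and p = 10%, a six-month window expects 0.15 tests. The depleted baseline gives 0.15 × (1 − 0.45) = 0.0825 per six months. The spurious difference is about 0.07 tests per person per six months.

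**Step 7, unscaled counts.** Comparing raw counts over 36 and 6 months gives a no-effect ratio of 0.17 to 0.24 in the simulations, an apparent fall.

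**Step 8, remedies.** A baseline from months 36 to 18 before selection gave a ratio of about 1.0 in every constant-rate scenario. A comparison group that passed the same filter, measured over the same two windows, carries the same artefact. The ratio of the two changes is then expected to be 1.0 if participation is unrelated to earlier monitoring.

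**The case against.** Several objections have force.

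- **The baseline is not empty.** A reader might infer that half of it is wiped out. The documents do not support that. Only normal UACR tests, and checks made at the same visits, are lost; elevated results and independent blood pressure, lipid, glucose or weight monitoring remain. The protocol does not list what counts as monitoring, so the dilution is unknown.
- **An apparent rise is not certain.** Neither section 9.1.2 nor section 11 says how the 3-year and 6-month windows are put on one scale. On raw counts, or as the percentage monitored at least once, the unequal windows dominate and the figure falls. At an assumed 0.5 contacts per year, with the baseline halved, 1 − exp(−0.75) = 53% are monitored before and 1 − exp(−0.25) = 22% after. The upward bias applies once rates are used.
- **Ratios of 1.7 to 1.9 rest on results varying by test.** Albuminuria class tends to persist (the cohort cited in section 2 found it stable in 79%), and fixed status lowers the ratio. Section 9.3 times follow-up from the study visit, which only patients with confirmed elevation attend. If they are the analysed group, the elevated share is higher and the artefact smaller. Section 4.3 is broader, so the population is unclear.
- **Section 4.3 plans a non-participant comparison.** That comparison does not use the depleted baseline. But it covers only the period after screening, and neither section 9.1.2 nor section 11 takes it up. Section 11 also calls patients left uninvited after a recent normal result eligible. If they counted as qualified, the comparator would be selected the opposite way (simulated no-effect ratio 0.91 to 0.95).
- **The pharmacy route is not shown to be free of the filter.** Its selection step in section 4.1 has none, but section 5.3 does not limit the exclusion to one route. A firm contrast between a biased and an unbiased route goes beyond the documents.

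**Conclusion.** The concern holds in limited form. In GP-route participants the filter takes normal UACR tests, and checks made at the same visits, out of exactly half of the baseline. On a per-person-year scale, endpoint 3 is therefore biased towards a rise when screening has no effect, and neither the endpoint definition nor section 11 guards against it.

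The direction was the same in every constant-rate scenario tried; the size cannot be fixed from the documents. Under the assumptions shown, the ratio is about 1.1 to 1.9 for UACR tests alone, depending on the elevated share and on whether status is fixed per person. For total monitoring it is about 1.04 to 1.05 when UACR tests are a tenth of contacts and 1.1 to 1.3 when they are half. It would be wrong to conclude that any observed rise must be artefact. The point is that the contrast as defined cannot separate the two. This is a secondary endpoint, and the change is worth making because it is cheap.

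**What to change.** In sections 9.1.2 and 11:

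1. Express monitoring per person-year in both windows.
2. Tie endpoint 3 to the section 4.3 comparator. Give the same before and after windows for invited non-participants who passed the same 18-month filter, leave out those uninvited because of a recent normal result, and compare the two changes.
3. For GP-route participants, also report the change from a baseline of months 36 to 18 before selection.
4. Show UACR testing separately from the other risk factors.

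The cost is wording and analysis. The months in question already lie inside the 3-year window, and section 4.3 already extracts data on non-participants, though that extraction must then cover their baseline too. The alternative baseline is shorter and older, with wider intervals, and may precede diagnosis in recently diagnosed patients, whose monitoring may then have been lower. The comparator cancels the artefact only if participation is unrelated to earlier monitoring. Reporting both lets the reader see whether they agree.

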#### Secondary endpoints

1. Unrecognized chronic kidney disease, defined as elevated albuminuria, not reported by the subject or previously recorded in electronic medical records of the subjects' general practice or pharmacy.
2. Persistent elevated albuminuria, defined as elevated albuminuria persisting despite good adherence (score  $\geq 4$  (doses seldom or never missed) reported in MARS) to treatment with RAS-inhibitors for at least 6 weeks prior to elevated albuminuria assessment.
3. Changes in frequency of cardiovascular risk factor monitoring, defined as the difference between the frequency of cardiovascular risk factor monitoring in participants 3 years before and 6 months after targeted albuminuria screening.
4. Changes in cardiometabolic drug prescriptions, defined as changes in any prescription for cardiovascular disease or CKD 6 months after targeted albuminuria screening compared to 3 years before.

**Nature and extent of the burden and risks associated with participation, benefit and group relatedness:** All selected subjects will be asked to participate on a free-will base and to send a signed informed consent form with a completed short questionnaire to GPRI. They will be

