#### **4.3 Phase 3: Implementation of care**

In phase 3 of the SALINE study we will determine if cardiovascular risk factor monitoring and cardiometabolic drug prescriptions changes within 6 months after participants have participated in the screening phases of the study. To this end, data about cardio-metabolic risk factor monitoring and prescriptions will be extracted from the database of the general practitioner and/or pharmacies involving all patients who qualified for the SALINE study (thus both those who participate in SALINE and those who did not). We will then determine

the frequency of cardio-metabolic risk factor monitoring and if drug prescriptions have occurred in the 6 months following the albuminuria targeted screening and compare those with participants who did not participate in SALINE.

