#### Implementation of care

After the study visits have been completed, data extractions from the general practitioners and/or pharmacies will be performed to retrieve data of cardiovascular risk monitoring and changes in cardiometabolic medication prescriptions from 6 months after the SALINE study visit of the participant.

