## **11 STATISTICAL ANALYSIS**

Characteristics of subjects recruited will be described as mean values with standard deviation or median with interquartile range for continuous variables. Categorical variables will be described as numbers and percentages of the subjects per category.

The overall prevalence of elevated albuminuria, and prevalences of unrecognized and persistent elevated albuminuria despite a RAS-inhibitor are described as percentages with 95% confidence intervals. The number of eligible patients from general practices who fulfilled the inclusion criteria but had an albuminuria level  $<3$  mg/mmol recorded within 18 months prior to selection (and where therefore not invited to participate), will be included in the denominator to calculate the prevalences.

To compare effectiveness and costs of screening on elevated albuminuria in pharmacies and in GP-care, the costs for the targeted screening strategies in both pharmacies and GPs will be calculated.

For each approach, all costs associated with the screening will be added and divided by the total number of subjects identified with confirmed elevated albuminuria. A screening-

approach will be considered more effective than the other if the costs per identified patient are  $\geq 10\%$  lower.

Frequencies of cardiovascular monitoring and treatment changes are summarized as numbers and percentages with 95% confidence intervals.

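### Secondary endpoint 3, and endpoint 4 on one reading, sets 36 months before screening against 6 months after it without scaling to person-time, so unchanged monitoring would look like a fall

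*Protocol*

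**What the plan says.** Section 9.1.2 of the protocol defines secondary endpoint 3 as a difference in monitoring frequency of "monitoring in participants 3 years before and 6 months after targeted albuminuria screening". The Summary gives the same definition: "the difference between the frequency of cardiovascular risk factor monitoring in participants 3 years before and 6 months after targeted albuminuria screening". Secondary endpoint 4 is defined as "changes in any prescription for cardiovascular disease or CKD 6 months after targeted albuminuria screening compared to three years before".

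The only analysis text for these outcomes is one sentence in section 11: "Frequencies of cardiovascular monitoring and treatment changes are summarized as numbers and percentages with 95% confidence intervals". The protocol nowhere defines frequency as a rate, annualises it or otherwise adjusts for the length of the observation period.

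Two other sections bear on the point:

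- Section 4.3 describes a different contrast. It will determine whether "drug prescriptions have occurred in the 6 months following the albuminuria targeted screening and compare those with participants who did not participate in SALINE".
- The implementation-of-care part of section 9.3 describes the extraction as covering monitoring and "changes in cardiometabolic medication prescriptions from 6 months after the SALINE study visit of the participant". It mentions no look-back of three years.

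**The concern.** A count of events, or the percentage of patients with at least one event, grows with the length of the window in which events are counted. Endpoint 3 takes the difference between a 36-month window and a 6-month window, and section 11 offers only measures of that kind. If the plan is followed as written, a practice that monitors its patients exactly as before will appear to monitor them less. A practice that monitors them more may still appear to monitor them less.

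Endpoints 3 and 4 carry secondary objectives 3 and 4. They also answer the last of the four novel aspects in the Summary, namely whether monitoring and treatment change after screening. An artefact of window length could therefore reverse the sign of a result that the study sets out to report.

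**Working it through.** The protocol gives no expected value, sample size or power for these endpoints, so there is no stated figure to reproduce. The check asks what the stated contrast shows when care does not change.

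**Inputs**

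- Window before screening: 3 years (section 9.1.2 and Summary).
- Window after screening: 6 months, or 0.5 year (same places).
- Summary measures: numbers and percentages (section 11).
- Rate of checks, r per year, the same before and after. The protocol does not give it, so a range of 0.5 to 12 per year is assumed.

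**Raw counts**

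Expected count = r × window length. The ratio after to before is (0.5 × r) / (3 × r) = 0.167, a fall of 83.3% whatever r is. At 1 per year this is 3 checks against 0.5; at 2 per year, 6 against 1. Care would have to rise 3 / 0.5 = 6-fold for the counts to show no change.

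**Percentage with at least one check**

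With checks at random times (Poisson, assumed), the proportion is 1 − exp(−r × window length). At 1 per year this gives 1 − exp(−3) = 95.0% before and 1 − exp(−0.5) = 39.3% after.

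| Assumed rate per year | Before (3 years) | After (6 months) | Apparent change, points |
|---|---|---|---|
| 0.5 | 77.7% | 22.1% | −55.6 |
| 1 | 95.0% | 39.3% | −55.7 |
| 2 | 99.8% | 63.2% | −36.5 |
| 4 | 100% | 86.5% | −13.5 |
| 12 | 100% | 99.8% | −0.2 |

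If checks instead follow a regular schedule, the proportion is the smaller of 1 and r × window length. That gives 100% against 50% at 1 per year, and 100% against 100% at 2 per year or more.

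**A true improvement**

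Suppose monitoring doubles after screening, from 1 to 2 per year. The Poisson percentages are 95.0% before and 63.2% after. The counts are 3 before and 2 × 0.5 = 1 after. Both show a fall.

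**Annualised rate**

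Count divided by window length is (3 × r) / 3 = r before and (0.5 × r) / 0.5 = r after. The expected difference is 0 at every rate.

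**Endpoint 4**

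The phrase "6 months after targeted albuminuria screening compared to three years before" can be read in two ways. If it compares prescribing status at two time points, window length plays no part. If it compares windows, counts of prescriptions or of prescription changes fall by the same 83.3%. The percentage with any prescription depends on how often prescriptions recur: repeat prescriptions at 4 to 12 per year fall in the last two rows of the table, while infrequent changes of treatment behave like the upper rows.

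**The case against.** The strongest reply is that frequency can mean events per unit of time. On that reading the artefact disappears, and a statistical analysis plan, which is not at hand, could say so. This stands in part: it is not certain that the analysis will show a spurious fall. But the window lengths are fixed in the protocol's own endpoint definition, and the one analysis sentence points to counts and percentages. An endpoint whose sign depends on an unstated unit is badly fixed.

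A second reply is that section 4.3 compares participants with non-participants over the same 6 months. That contrast is free of the window problem, whatever confounding it carries. It is not the defined endpoint, however, and does not repair it. The two descriptions need reconciling.

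Third, the size of the artefact in the percentages depends on the assumed rate and timing. That is correct: it is large at 0.5 to 2 random checks per year, small at 12, and absent on a regular schedule of 2 or more per year. The fall in counts does not depend on the rate.

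A reader might also infer that both endpoints are equally affected. The text does not support this, because endpoint 4 allows a time-point reading. Nor does it support dismissing a yearly rate because an annual check falls in only one half of the year. Over a cohort that adds variability, and it adds bias only if screening dates line up with the check-up season, of which the protocol gives no sign.

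**Conclusion.** The point holds for endpoint 3, and for endpoint 4 if three years before is a window. Summarised as section 11 says, unchanged monitoring would appear as a fall of 83% in raw counts. In the percentage with at least one check it would appear as a fall of about 56 points at an assumed 0.5 or 1 per year, 36.5 points at 2 and 13.5 points at 4, under Poisson timing. The rates are assumptions; the 6:1 ratio of windows is the protocol's own.

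A reader might conclude that a false fall is certain, or that the study would have no valid evidence on change in care. Neither follows, because an annualised rate would be unbiased under unchanged care and section 4.3 offers a same-window comparison. These are descriptive secondary endpoints with no stated hypothesis test, and neither primary endpoint is affected. The definition should be fixed before the data are analysed, but it does not threaten the study's main results.

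**What to change.** Amend sections 9.1.2 and 11 and the Summary as follows.

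- **Endpoint 3.** Define monitoring frequency as events per person-year, and report a before-after rate ratio or difference with a 95% confidence interval that accounts for pairing within patients. For any percentage with an event, use equal 6-month windows, for example the same calendar months in the preceding years.
- **Endpoint 4.** State whether three years before is a window or a time point. If it is a window, compare the proportion with a start, stop or change of a prescription over windows of equal length.
- **Index date.** Use one. Section 9.1.2 counts from the albuminuria screening and section 9.3 from the study visit. Only subjects with elevated albuminuria are invited to a visit, so a visit date does not exist for the other participants or for the non-participants in section 4.3.
- **Extraction.** Write the 3-year look-back into section 9.3. The endpoints imply it, but sections 4.3 and 9.3 describe only data after screening or after the visit.
- **Section 4.3.** State how the comparison of participants with non-participants relates to the before-after endpoints, and which of the two answers secondary objectives 3 and 4.

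The cost is mainly rewording. The look-back adds no data beyond what the endpoints already require, but it must be covered by the extraction as described.
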